## Abstract

Diseases of the larynx and trachea are a heterogenous group of disorders. Their diagnosis frequently requires invasive methods. Ultrasound is a non-invasive, repeatable and safe diagnostic method, which has recently, thanks to the development of technology, provided for very accurate imaging of even small structures, as well as their assessment on dynamic examination. Ultrasound examination of the larynx and trachea will be performed in 2022–2023 in a group of randomly selected 300 stable neonates born between 32 and 42 weeks of gestation. The results of this study will be presented after data collection in accordance with the adopted methodology. To date, this will be the first study to describe the ultrasound anatomy of the larynx and trachea and to establish reference ranges for the size of individual structures of the larynx and trachea in the neonatal population. We expect that our study will contribute to the further development of this part of ultrasonography and will reduce the number of invasive procedures performed in the diagnostics of these organs in the future. This manuscript is a study protocol registered at ClinicalTrials.gov (Identifier NCT05636410) and approved by the Bioethics Committee of the Medical University of Warsaw (KB 65/A2022).

## 1. Introduction

Diseases of the larynx and trachea constitute a heterogenous group of disorders. They may include congenital anatomical disorders, neoplastic changes, vocal cord paralysis of varied aetiology or narrowing of the larynx associated with long-term intubation. The multitude of disorders of these organs necessitates the continuing search for diagnostic methods which will not only provide answers to clinical questions, but will also be safe and have the least level of interference with the wellbeing of the patient.

Diagnosis of diseases of the larynx and trachea with respect to neonates and infants is mainly based on endoscopy, magnetic resonance imaging and computer tomography. There are some challenges associated with these investigations which result in them being rarely used in everyday practice. One challenge concerns the invasiveness of the procedure during endoscopy of the upper respiratory tract or ionizing radiation in CT. Others include the not infrequent necessity of anaesthetizing the patient and the need to obtain special parental consent for the procedures, which is also not without significance. Moreover, the application of these techniques requires high numbers of highly qualified specialists for their performance and evaluation. Finally, an important constraint is the limited availability of fiberoscopy, MRI or CT in most neonatal departments, which results in the necessity of transporting the patient to another facility.

In recent decades, only a few studies have been reported which described the ultrasound anatomy of the larynx in pediatric populations, especially in diagnosis of infant laryngomalacia prior to and following intubation or that of the mobility of the vocal cords [1,2,3,4,5,6]. Some of the studies which involved small groups of subjects—intensive care unit patients—were performed using lower quality ultrasound devices or addressed only part of the larynx and thus did not provide for unequivocal conclusions to be drawn [6,7,8,9,10]. In the literature, there are also reports where ultrasonography is used to assess pathologies such as laryngeal cysts or paralysis of the vocal folds [11,12]. To date, no standards have been published concerning the size of the structures of the larynx and trachea or the mobility of the vocal cords on ultrasound examination in the neonate. Additionally, there are no studies describing the technique of ultrasound examination of these organs with respect to the neonates, which would cover all relevant aspects, starting from a comfortable position for the patient, through the assessment of individual levels of the larynx, and ending with the description of the norms of the size of the structures of the larynx and trachea based on a large group of neonates. Additionally, there are no recommendations which include ultrasound examination as a reliable component of the diagnosis of congenital disorders of the larynx or other diseases of this organ in the pediatric population. With regard to adult patients, in the literature we can find high-value descriptions of ultrasound anatomy of the larynx using high-resolution ultrasonography [13]. Ultrasound is a non-invasive, repeatable and safe diagnostic method, which has recently provided for very accurate imaging of even small structures. Furthermore, the easy availability of this examination may in the future contribute to the early diagnosis of diseases of the larynx and trachea without the need to prolong neonatal hospitalization, anaesthesia or transportation of the patient.

We plan to provide a complete ultrasound examination standard for the larynx and trachea. Initially, the study will describe the preparation of the office, the exact placement of the neonate and the examination technique that will least affect the patient’s comfort. Subsequently, the focus will be placed on determining the size and mobility standards of specific parts of the larynx and trachea in neonatal populations. Additionally, we plan to prepare an examination protocol of those organs to unify the results with other future studies. The expectation is that this protocol will allow clinicians to learn about laryngeal ultrasound and will allow other researchers to perform similar studies in other pediatric populations, as well as size and mobility standards of specific parts of these organs in the neonatal population. In addition, the use of neural networks to analyze the ultrasound images obtained will provide for the development of algorithms which could become an irreplaceable tool, not only in the diagnosis of disorders, but also in predicting disorders affecting further development of a newborn.

## 2. Experimental Design

The design is a prospective, multi-center cohort study. The trial protocol was approved by the Bioethics Committee of the Medical University of Warsaw on 10 October 2022 (decision number KB 65/A2022) and has been registered at ClinicalTrials.gov (Identifier-NCT05636410). Once the eligibility criteria are fulfilled and written consents are obtained, the newborns will undergo an ultrasound examination according to the established protocol. After examination, the captured images will be analyzed prospectively by researchers in a computer program to collect data on the dimensions of particular structures. Additionally, data obtained from each patient will be analyzed with the use of neural networks in order to develop artificial intelligence algorithms. The study design diagram is shown in Figure 1.

## 3. Materials and Equipment

Ultrasound examination of larynx and trachea will be performed in the Department of Neonatology and Neonatal Intensive Care at the Medical University of Warsaw and the Department of Neonatology at Ujastek Medical Center in Cracow, in 2022–2023, in a group of three-hundred randomly selected neonates, born between 32 and 42 weeks of gestation, who are stable and do not require intubation. The examination will take place in a specially prepared ultrasound room; therefore, only stable newborns who do not require intubation will be included. Prior to that, written consent will be obtained from at least one parent prior to the examination.

Inclusion criteria:Gestational age ≥32 weeks.

Exclusion criteria:Gestational age <32 weeks;Presence of significant congenital anomalies;Intubated neonate;Unstable neonate.

As recommended by WHO for similar research projects, a representative study group should include at least 200 study participants [14]. To improve the quality and reliability of the results, the number of participants for this study was set at 300. The calculated inter-observer and intra-observer concurrence (Kappa coefficient) will be calculated for all measurements.

The examination will be performed with high-class ultrasound machine (Philips Epiq 97G device, using the eL18-4 linear probe), using water-based, hypoallergic ultrasound gel (Aquasonic 100, Parker laboratories Inc., Fairfield, CT, USA), previously warmed to body temperature.

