
In order to reduce the variability of the results, only measurements taken from patients who are breathing calmly will be considered. Crying, anxious or heavy breathing patients will be marked and will not be included in the measurements. These patients will not be excluded from the study to determine the percentage of patients who can be examined without compromising comfort in this population.

In addition to the data obtained from the ultrasound examination, the following patient information from the medical history will be collected: date and time of delivery, gestational age, age at the time of the study, Apgar score at the 1st, 5th and 10th minutes of life, gender, type of delivery, birth weight and length, weight on the day of the examination.

During the next stage of the study, the images acquired in the ultrasound examination will be analyzed with the use of neural networks in order to develop artificial intelligence algorithms. The method of these analyses will be determined at a later date, depending on the quality and quantity of information collected.

To date, there is no established standard technique for ultrasound examination of the larynx and trachea with respect to newborns. Furthermore, at the time of designing and commencing the study, there is no reference standard that would allow one to compare the obtained results.

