### 4.2. Analysis

Statistical analysis will be conducted using R software, version 4.2.1. or later. Norms for measurements of the larynx and trachea will be defined with the following percentiles: 5th, 10th, 25th, 50th (median), 75th, 90th and 95th. Additionally, density charts will be drafted to visualize the distribution of data for each measurement. Normality of distribution will be assessed using the Shapiro–Wilk test and based on visual assessment of histograms. Differences in each measurement between subgroups (sex, Apgar score, delivery method) will be verified using t-test and ANOVA or their non-parametric equivalents, as appropriate. Correlation analysis will be conducted between measurements of the larynx and trachea and gestational age, age at the time of the study, Apgar score at the 1st, 5th and 10th minutes of life, gender, type of delivery, birth weight and length, and weight on the day of the examination. Additionally, regression analysis (univariate and multivariate) will be used to determine the relationship between the above anthropometric measurements and measurements of the larynx and trachea.

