## 5. Expected Results

The main aim of the study is the accurate description of the ultrasound anatomy of the larynx and trachea, as well as the establishment of an examination standard for these organs in neonatal populations. The next objective is to set reference ranges for the size of individual structures of the larynx and trachea with respect to newborns. The study also aims to develop a universal method of ultrasound assessment of the mobility of the vocal cords on dynamic examination and to determine a rule for predicting the expected size of the laryngeal and tracheal structures in relation to anthropometric measurements.

Another purpose of the study is to promote the use of a non-invasive examination, such as ultrasonography, in the diagnosis of diseases of the larynx and trachea with respect to the youngest patients. Additionally, the study will be conducted to develop artificial intelligence algorithms based on artificial neural networks, which will allow one to make larynx and trachea diagnostics easier in the future.

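### Eligibility turns on current intubation only and intubation history is not a listed data item, so stable infants extubated before the scan can enter the reference sample unidentified

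*Protocol article*

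**What the plan says.** Section 3 (Materials and Equipment) has one inclusion criterion, "Gestational age ≥32 weeks". Apart from gestation below 32 weeks, the exclusions are "Presence of significant congenital anomalies;Intubated neonate;Unstable neonate". The reason for the intubation criterion is practical. The scan is done in a dedicated ultrasound room, "therefore, only stable newborns who do not require intubation will be included". One of the two recruiting units is the "Department of Neonatology and Neonatal Intensive Care at the Medical University of Warsaw".

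The Introduction, in describing the diseases of these organs, includes "narrowing of the larynx associated with long-term intubation".

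Section 4.1 states that "the following patient information from the medical history will be collected" and then itemises it: delivery date and time, gestational age, age at the scan, Apgar scores, sex, mode of delivery, birth weight and length, and current weight. Previous intubation or ventilation is not in that list. The same section restricts the measurements to infants who are breathing calmly.

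The sample serves as a norm set. Section 5: "The next objective is to set reference ranges for the size of individual structures of the larynx and trachea with respect to newborns". Section 4.2: "Norms for measurements of the larynx and trachea will be defined with the following percentiles: 5th, 10th, 25th, 50th (median), 75th, 90th and 95th".

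**The concern.** A reference range for a normal structure should come from infants in whom that structure is unaffected, or should at least allow affected infants to be separated. Here the intubation criterion serves logistics and stability, not normal anatomy. An infant who was intubated for some time, extubated and is now stable meets every listed criterion, yet carries an exposure that the article itself associates with laryngeal narrowing.

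If such infants have smaller airway dimensions, they sit in the lower tail and pull the published 5th percentile outward. Fewer than 5% of unaffected infants then fall below it, and a later infant with a narrowed airway is less likely to be flagged. Because the history list omits the exposure, the listed data cannot show whether this has happened, and no later analysis of those data could correct it.

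**Working it through.** **Step 1: does the text let these infants in?**
- Section 3 excludes the intubated neonate. Its stated reason (the ultrasound room) and its present-tense wording in "therefore, only stable newborns who do not require intubation will be included" point to current status.
- The stability and congenital-anomaly exclusions do not remove a stable infant with a past intubation and no malformation.
- The calm-breathing rule in section 4.1 removes crying, anxious or laboured infants. It does not remove a calm, previously intubated one.
- The history list in section 4.1 has no intubation or ventilation item, so such infants cannot be identified from it.

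The text therefore admits them, and nothing listed flags them.

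**Step 2: how large could the effect be?** The plan has no figure to reproduce. The 300 is set above a cited minimum of 200, without precision inputs. What follows is an illustration.

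Inputs:
- n = 300 (section 3).
- Target percentile p = 0.05 (section 4.2).
- Share e of previously intubated infants: not in the documents; assumed 1% to 10%.
- Narrowing d in SD units, uniform in those infants: not in the documents; assumed 0.5 to 2.
- Normal distribution with equal SD in both groups: assumed.

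The published 5th percentile q solves

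(1 − e)·Φ(q) + e·Φ(q + d) = 0.05,

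and the shift is q − (−1.645). The share of unaffected infants below q is Φ(q).

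Check for e = 0.05, d = 2: q = −1.954, Φ(−1.954) = 0.0254 and Φ(0.046) = 0.518. Then 0.95 × 0.0254 + 0.05 × 0.518 = 0.0241 + 0.0259 = 0.050. The shift is −1.954 + 1.645 = −0.309 SD.

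Shift of the 5th percentile in SD, with the share of unaffected infants below it in brackets:

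| e (infants of 300) | d = 0.5 | d = 1 | d = 2 |
|---|---|---|---|
| 1% (3) | −0.007 (4.92%) | −0.020 (4.79%) | −0.058 (4.43%) |
| 2% (6) | −0.015 (4.85%) | −0.040 (4.60%) | −0.119 (3.89%) |
| 5% (15) | −0.036 (4.64%) | −0.099 (4.06%) | −0.309 (2.54%) |
| 10% (30) | −0.071 (4.31%) | −0.191 (3.32%) | −0.622 (1.17%) |

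**Step 3: comparison with sampling error.** The standard error of a nonparametric 5th percentile is √(p(1 − p)/n) / φ(z_p). With n = 300: √(0.05 × 0.95 / 300) = 0.0126, φ(−1.645) = 0.103, ratio 0.122 SD. This assumes that all 300 are measured. Infants who are not calm are left out, so the actual standard error would be somewhat larger (0.149 SD at n = 200).

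At 1% the shift stays below the standard error throughout. At 2% it reaches about the same size only for 2 SD. It clearly exceeds the standard error at 5% with 2 SD, and at 10% with 1 SD or more.

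**The case against.** The strongest reply is that the problem may be negligible. The documents do not say how many eligible infants will have been intubated, and with few of them or mild narrowing the shift is well inside sampling error. That stands. It limits the size of the point but does not answer it, because without the history item nobody can tell which row of the table applies.

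Three stronger readings are tempting, and the documents do not support them:
- That intubation of any kind is a named cause of narrowing. The Introduction speaks of long-term intubation and of an association. Infants intubated briefly are not clearly covered, which is why duration should be recorded.
- That such infants do enter the sample, mainly at the preterm end. The intensive care setting and the 32-week limit make it plausible, but no count is given, and section 4.2 names no gestational bands within which contamination would concentrate.
- That every measurement is affected. Several dimensions in section 4.1 run between external cartilage margins, and the only one called a lumen is tracheal, whereas the Introduction speaks of the larynx. Nor do the documents say that soft-tissue thickness rises after intubation.

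The exclusion could also be read as ever intubated. The ultrasound-room reason argues against that; if it was meant, the text should say so. The calm-breathing, stability and anomaly rules would remove some symptomatic infants, but not a symptom-free infant with a past intubation.

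Finally, an article condenses a fuller protocol, and further case-report fields may exist there. But the article prints both the eligibility list and the history list, and neither addresses the exposure.

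**Conclusion.** The point holds as a gap in eligibility and data capture. Stable infants extubated before the scan can enter the sample that defines the norms, and the listed data cannot identify them. This sits badly with the article's own naming of narrowing after long-term intubation as a disease.

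The size is unknown. Under the assumptions above, the outward shift of the 5th percentile is about 0.01 to 0.06 SD at 1% contamination, 0.04 to 0.31 SD at 5% and 0.07 to 0.62 SD at 10%, against a standard error of about 0.12 SD. In the 5%, 2 SD case only about 2.5% of unaffected infants, not 5%, would lie below the published limit. These figures show what the gap could cost. They are not an estimate of bias in this study. Unlike sampling error, a bias of this kind would not shrink with a larger sample of the same composition.

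**What to change.** Either of two changes would close the gap:
1. State in section 3 that, for the reference sample, the criterion covers previous as well as current intubation.
2. Add to the history list previous intubation (yes/no, with duration) and airway disease clinically known before the scan. Compute the primary norms without these infants and report the norms with them as a sensitivity analysis.

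The second option keeps all infants in the study and shows directly whether the choice matters.

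Infants should not be dropped because of how the larynx or trachea looks on the scan being normed, unless the criteria are defined beforehand. Section 4.1 says that no reference standard exists, so unplanned removal would be circular and could trim the tails.

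The cost is a short amendment, one or two chart fields and a few infants fewer in the norm set. For infants already scanned, the fields could be completed from the charts only if the study code can still be linked to the record. Section 4.1 describes coded, anonymous collection, so that needs checking.

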
In every case, during further evaluation, the researcher who carried out the ultrasound examination and other researchers with at least 5 years’ experience in ultrasonography will take the following measurements using the dedicated software (Horos, Nimble Co. LLC d/b/a Purview, Annapolis, MD USA):Width of the larynx at the level of the glottis (measurement taken in the transverse plane from the external margins of the thyroid cartilage) (Figure A2);Depth of the larynx at the level of the glottis (measurement taken in the transverse view from the external margin of the thyroid cartilage to the external border of the annular cartilage) (Figure A2);Thickness of the thyroid cartilage in the midline and on both sides transversely at the level of the glottis (in the transverse plane measurement from external margins of thyroid cartilage and vertical measurement of thyroid cartilage above the anterior commissure at the level of well-visualized arytenoid cartilages in the transverse plane) (Figure A3);Angle formed by the lamina of the thyroid cartilage (measurement taken in the transverse plane with two lines drawn tangentially to the thyroid laminae) (Figure A4);Width of the glottis during calm breathing (measured in the transverse plane with lines drawn between two medial margins of arytenoid glands when they are farthest apart during breathing) (Figure A5);Angle formed by the vocal cords during calm breathing, considering the opening angle of individual chords (measurement taken in the transverse plane with a line drawn from posterior part of the anterior commissure to the medial margins of the arytenoid gland) (Figure A6);Surface area of the glottis during calm exhalation (in order to avoid distorting the result of measuring the glottal area using the outline of its visible borders, this measurement will be taken by calculating the area of a triangle, the basis of which will be the width of the glottis, and the height will be the depth of the glottis measured from the posterior part of the anterior commissure to the line drawn to measure glottis width, measurement taken in the transverse plane) (Figure A7);Thickness of the arytenoid muscle during inhalation and exhalation (measurement taken in the transverse plane in the midline from the outer surfaces of this muscle) (Figure A8);Thickness of the vocal cords in transverse projections, tangentially to the midline (measure in the transverse, lateral plane, ventral and tangentially to the arytenoid cartilages) (Figure A9);Amplitude and duration of vocal cord movement during breathing at rest (measurement taken in the transverse, lateral plane, using M-mode as the distance between two lines drawn by the movement of the outer surface of the vocal cord—lighter than the surrounding lines);Width and depth of the trachea (measurement taken in the transverse plane of the longest transverse dimension of the trachea from the external edges of the tracheal cartilages and measurement of the longest depth of the trachea from the external margin of the tracheal cartilage to the outer part of the membranous wall) (Figure A10);Width and depth of the tracheal lumen (measurement made in the transverse plane of the longest transverse dimension and longest depth of the hypoechoic area limited by the inner edges of the tracheal cartilages and membranous wall of the trachea) (Figure A11);Thickness and width of the supraglottis (measurement taken in the transverse plane of the thickest and the widest visible part of the supraglottis) (Figure A12);Thickness of the preepiglottic space (measurement taken in the transverse plane of the thickest part) (Figure A13);Thickness of the infrahyoid muscles at the level of the thyroid cartilage and hyoid bone (measurement taken in the transverse view of the thickest dimension between the outer edges of thyrohyoid and sternohyoid muscles as a group of infrahyoid muscles in the transverse plane, at the level of well-visible hyoid bone and glottis) (Figure A14).

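### Observer agreement on quantitative measurements is to be summarised by a kappa coefficient with no categories or weights, a statistic that does not suit them and gives no reading error in the measured unit

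*Protocol article*

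**What the plan says.** - **The statistic.** Protocol article, section 3 (Materials and Equipment): "The calculated inter-observer and intra-observer concurrence (Kappa coefficient) will be calculated for all measurements". One statistic is named for both kinds of agreement, and its scope is every measurement.
- **What is measured.** The list in section 4.1 (Test Methods) consists of quantities. Examples are "Width of the larynx at the level of the glottis", "Angle formed by the lamina of the thyroid cartilage", "Surface area of the glottis during calm exhalation" and "Amplitude and duration of vocal cord movement during breathing at rest". The other items are further widths, depths, thicknesses and an angle. None is a rating or a class.
- **Who measures.** Section 4.1 assigns the readings to "the researcher who carried out the ultrasound examination and other researchers with at least 5" years of ultrasound experience, working in dedicated software on the recordings. Section 6 (Discussion) adds that the other researcher reads independently and without the patient history.
- **How the values are analysed.** Section 4.2 (Analysis): "Norms for measurements of the larynx and trachea will be defined with the following percentiles", from the 5th to the 95th. It continues: "Additionally, density charts will be drafted to visualize the distribution of data for each measurement". Shapiro-Wilk tests, t-tests or ANOVA (or non-parametric equivalents), correlation and regression follow.

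The article gives no categories, cut points, kappa weights or recording precision. It names no ICC, limits of agreement or other measure of reading error.

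**The concern.** Kappa compares how often two readings fall in the same category with how often they would do so by chance. It needs categories, and these measurements have none. That leaves three ways to carry out the plan as written:

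1. Treat each recorded value as its own category. Only exact ties then count as agreement, so a difference of 0.1 mm scores the same as one of 5 mm.
2. Bin the readings first. The result then depends on cut points that the article does not state.
3. Use weights. The result then depends on a weighting scheme that the article does not state.

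Section 6 accepts that images and measurements may differ considerably between researchers. Section 5 makes reference ranges an objective. A clinician who compares one infant with a 5th or 95th percentile needs to know how far a second reading of the same image might lie from the first, in the unit of the measurement. Kappa does not report that in any form. At stake is whether the reported agreement can be interpreted, and whether similar studies can be compared with it.

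**Working it through.** The plan states no kappa value, target or precision, so there is no figure of its own to reproduce. The check asks what kappa returns when true agreement is held fixed and only the recording step changes.

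**Inputs**
- From the document: n = 300 (section 3); independent reading by a second researcher (section 6); quantitative measurements (section 4.1).
- Assumed, because the document gives no value: normal true values, independent reader errors, no systematic offset between readers, true ICC of 0.75 to 0.99, recording step of 0.01 to 1 SD.

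**Step 1: reader error.** With between-infant SD = 1, reader error SD = √((1 − ICC)/ICC). At ICC 0.95 this is √(0.05/0.95) = 0.229.

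**Step 2: hand check for a small step h.** Kappa = (p_o − p_e)/(1 − p_e).
- Observed ties: the difference between two readings of one infant has SD √2 × 0.229, so p_o ≈ h/(2 × 0.229 × √π). For h = 0.1, p_o ≈ 0.123.
- Chance ties: a single reading has SD √(1 + 0.0526) = 1.026, so p_e ≈ h/(2 × 1.026 × √π). For h = 0.1, p_e ≈ 0.0275.
- Kappa ≈ (0.123 − 0.0275)/(1 − 0.0275) ≈ 0.098.
- For h = 0.01, kappa ≈ (0.0123 − 0.00275)/(1 − 0.00275) ≈ 0.0096.

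For small steps kappa is roughly proportional to the step, so it tends to zero as recording gets finer.

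**Step 3: simulation at true ICC 0.95** (two readers, 300 infants). For steps of 0.01, 0.1, 0.5 and 1 between-infant SD, unweighted kappa averages about 0.01, 0.10, 0.44 and 0.64. The last figure varied between 0.64 and 0.65 across runs. The first two match the hand check.

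**Step 4: range over the assumed ICC.** Here the step is a fraction of the SD of a single reading (infant plus error). At ICC 0.95 this scale differs from the one above by a factor of √0.95 = 0.97. Entries are mean unweighted kappa over 100 replicates.

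| True ICC | Step 0.01 SD | 0.1 SD | 0.5 SD | 1 SD |
|---|---|---|---|---|
| 0.75 | 0.004 | 0.03 | 0.15 | 0.30 |
| 0.90 | 0.005 | 0.06 | 0.31 | 0.51 |
| 0.95 | 0.008 | 0.10 | 0.45 | 0.65 |
| 0.99 | 0.03 | 0.25 | 0.74 | 0.84 |

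Across each row the readers agree equally well, yet kappa changes by a factor of about 30 or more. A true ICC of 0.75 recorded at 1 SD (0.30) scores higher than a true ICC of 0.99 recorded at 0.1 SD (0.25).

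**Step 5: alternatives on the same simulated readings.**
- ICC (two-way random effects, absolute agreement, single rater) returned 0.75, 0.90, 0.95 and 0.99 at the 0.01 SD step. At the 1 SD step it fell as well, for example to 0.88 when the true value was 0.95, but far less than kappa did.
- Quadratic-weighted kappa matched that ICC to within 0.001 in every cell.
- Limits of agreement stay in the measured unit. At ICC 0.95, in single-reading SDs, error SD = √0.05 = 0.224, so the limits are ±1.96 × √2 × 0.224 = ±0.62.
- A constant offset of 0.5 SD between two readers adds 0.5²/2 = 0.125 to the variance. The ICC becomes 0.95/(0.95 + 0.05 + 0.125) = 0.84, and the limits are centred 0.5 SD from zero, so the bias is visible.

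**The case against.** The strongest reply is that the article says only kappa, without calling it unweighted. With quadratic weights it would nearly equal the ICC, as step 5 shows. That stands, and it confines the tie-counting criticism to the unweighted form. It does not rescue the plan as written: no weights are stated, and weighted kappa is still a unitless index with no reading error in the measured unit.

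Four stronger readings are tempting, but the document does not support them.

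- **Kappa will come out near zero.** This is so only for unweighted kappa on finely recorded values. With steps that are large relative to the spread, which is possible for thin structures, the simulation gives values up to 0.84. The article states neither spread nor recording step.
- **No second reading exists for the intra-observer figure.** The article does not say that each reader measures once. Promising intra-observer agreement presupposes repeat readings, and the recordings are archived. The details of re-reading may properly sit in the full protocol or analysis plan.
- **This agreement is the only evidence that the examination can be reproduced.** One researcher scans and the readers measure the stored recordings. Agreement here concerns the reading of fixed images, and an ICC would not show reproducibility of the scan either.
- **The reference ranges are compromised.** The percentiles, subgroup tests and regressions in section 4.2 do not use kappa.

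It could also be said that a condensed article leaves such matters to the analysis plan. That would excuse silence, but the article names a specific statistic for all measurements.

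**Conclusion.** The point holds in this form: section 3 names kappa, with neither categories nor weights, for measurements that sections 4.1 and 4.2 treat as continuous. In its unweighted form the result is driven largely by recording precision. At an assumed true ICC of 0.95 it runs from about 0.01 to about 0.64 as the step goes from 0.01 to 1 between-infant SD. These sizes rest on normal values, independent errors, no reader offset, and assumed ICCs and steps. The mismatch between statistic and data does not depend on those assumptions.

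Severity is should-fix. Agreement is a supporting analysis, the norms do not depend on it, and the same paired readings can be reanalysed with a suitable method at any time.

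**What to change.** In section 3, replace the parenthesis naming kappa with wording to this effect:

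- For each continuous measurement, inter-observer agreement is reported as the ICC for absolute agreement (two-way random effects, single rater) with 95% CI, together with the Bland-Altman bias and 95% limits of agreement in the measured unit.
- Intra-observer agreement is reported in the same way, with the within-observer SD in the measured unit.
- Kappa is kept only for genuinely categorical ratings, if any are made, such as whether a structure is visible.

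It should also say that these figures describe the reading of stored images. The cost is a wording change and a few lines of R, which section 4.2 already specifies. No further infants or scans are needed.
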